### Aims

Healthy newborns born in the hospital, observed for low probability of neonatal infection will be compared to newborns exposed to antibiotic therapy in early life (first 1–2 weeks) by investigating potential differences in fecal microbiota composition. For this purpose fecal bacterial composition and diversity is determined at eight time points during the first year of life, from birth on: day one (T1), day two (T2), one week (T3), two weeks (T4), one month (T5), three months (T6), six months (T7), one year (T8). An overview of the sample time points and outcomes is shown in Fig. 1.

**Fig. 1 Fig1:**
[figure not shown]
Overview of the sample time points and outcomes

Potential differences in proportions (abundance and diversity) of intestinal bacterial groups (phyla) and species in antibiotic treated infants versus healthy controls will be determined by use of 16S-23S rRNA gene analysis. Secondly, we investigate differences in clinical outcomes between infants treated with antibiotics and controls. We evaluate incidences of atopic dermatitis (eczema), food allergy, upper respiratory tract infections (URTI), lower respiratory tract infections (LRTI), gastrointestinal infections (GITI) and excessive crying, prospectively assessed by parental reports and retrospectively assessed by doctor’s diagnoses. The clinical endpoints will be linked to the developing intestinal microbiota during the first year of life. Body mass index and standard deviation (SD)-scores are calculated from individual weight and height curves.

Parents of all included infants will report the use of antibiotics (type of antibiotics and duration of treatment) during the complete study period (i.e. the first year of life) on the calendar lists. Moreover, (the type of) prescribed antibiotics will be investigated at the end of the initial study period by approaching the infant’s pharmacy on medications used in the first year of life. Parents are also asked to report the moment of stool collection (date) on the collection vial, so the investigators can calculate the time between antibiotic treatment and stool sample collection. We hypothesize that in early life antibiotic treated infants develop more eczema during their first year than non-antibiotic treated infants (healthy controls). We also expect an increase in incidence of (parental reported as well as doctor’s diagnosed) food allergy, respiratory tract infections (RTI’s) and gastrointestinal tract infections (GITI’s) in infants treated with antibiotics compared to controls.

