#### Collection of fecal samples

Parents collect a total of 8 fecal samples during the first year of life, and one sample at or around the 2^nd^ birthday of the child. Directly after birth, nurses of the maternity and neonatal wards collect the first fecal samples, which are frozen at −20 °C. After discharge the parents start collecting samples at home. Collection of stool samples is standardized (oral instruction by the investigators at time of inclusion and there is a written instruction on the daily checklist of symptoms, that parents receive).

Parents are instructed to sample directly from the diaper by means of stool collection vials (with integrated spoons), and immediately freeze them in their home freezers at a temperature of −18 to −20 °C. Moreover, in order to be able to study transmission of microbiota from the parents to the child, mother collects a stool sample of her own within the first week after the delivery and a buccal mucous membrane swab and a skin swab from the mother and the father are taken at inclusion.

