### Statistical analysis

We will evaluate the potential relationships between antibiotic use in early life and the various (clinical) endpoints. Variables are verified for normal distribution and *t*-tests will be used for testing the null hypothesis. Either logistic regression analysis or cox regression analysis will be applied to the data (appearance of the primary endpoint(s) will be recorded as specifically as possible), so that odds ratios or hazard ratios and their 95 % confidence interval can be presented for description of the relationships. Multivariate models will be used to assess confounders and confounding effects. We will perform post hoc analyses to look for potential effects of the different antibiotic regimes. Outcomes may, possibly, be classified into subgroups. According to antibiotic treatment after the first two weeks, children will be grouped based on the number of antibiotic courses during the first year of life (0 / 1 / 2 or more courses). Within the ‘treatment groups’ a distinction can be made between the class or spectrum of the prescribed antibiotics.

Microbiota composition will be described by means of abundance, diversity and (dis)similarity. Diversity is calculated using the Shannon index [42] and differences in this index will be tested with Mann–Whitney *U* test. Dissimilarities between samples, or between-sample diversity, are calculated as the cosine distance between each pair of samples and analyzed with principal coordinate analysis (PCoA). All statistical analysis will be conducted using SPSS version 22.0 (SPSS Inc., Chicago, IL, USA) and the vegan software package in R (Foundation for Statistical Computing, Vienna, Austria).

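### Stool samples are compared at nominal ages with tests that carry no age term; actual age at sampling can be derived in both groups and should enter the microbiota comparison

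*Protocol article*

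**What the plan says.** Under Aims, the microbiota comparison comes first and the clinical outcomes second. There, "fecal bacterial composition and diversity is determined at eight time points during the first year of life", running from day one (T1) and day two (T2) through one week, two weeks, one month, three months and six months to one year (T8). The article states no windows around these ages.

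Still under Aims, below Fig. 1: "Parents are also asked to report the moment of stool collection (date) on the collection vial", and the reason given is "so the investigators can calculate the time between antibiotic treatment and stool sample collection". The same paragraph has antibiotic use recorded for every infant over the whole first year.

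Under Collection of fecal samples, ward nurses take the first samples. Then: "After discharge the parents start collecting samples at home".

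Under Statistical analysis, the second paragraph covers the microbiota. For the Shannon index, "differences in this index will be tested with Mann–Whitney" U. Dissimilarity is measured as cosine distance and examined by principal coordinate analysis. The multivariate models for confounding appear in the first paragraph, with the odds and hazard ratios for the clinical endpoints. Age at sampling is not named there.

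**The concern.** The Background describes the intestine as virtually sterile at birth and colonised from then on, so age should matter to the microbiota, above all where the schedule is tightest (T1 to T4). A sample labelled one week need not have been taken on day seven, and the Mann–Whitney test treats all samples with the same label as equal in age.

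The one derived time variable that the article mentions does not help the group comparison. Time since the early-life course exists for treated infants and not for controls. Age in days exists for both, but the article gives it no role.

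Two consequences follow. If mean age at a time point differs between the groups, the test mixes age with exposure. If ages merely scatter to the same degree in both groups, the comparison stays valid but loses precision, because variation due to age remains in the residual.

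**Working it through.** **Could ages differ by group?** The article gives no ages at collection, so this can only be reasoned from the text.

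- Controls are observed for 24–48 h (Study design and population).
- Treated infants enter through admission to the neonatal ward for antibiotic treatment (Inclusion and exclusion criteria). Their length of stay is not given.
- The change from nurse to parent happens at discharge (Collection of fecal samples).

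The moment of handover therefore depends on length of stay, which may differ by group. A change of collector does not in itself establish a change in timing. A difference is plausible, of unknown direction and size.

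**What would a difference do to the named test?** The article states no figure on this point to reproduce. The calculation below is an illustration.

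Inputs:
- 150 treated, 300 controls and 15% dropout (Power calculation): 150 × 0.85 = 127.5, taken as 127, and 300 × 0.85 = 255. This assumes that the dropout applies equally to both groups and that every remaining infant supplies the sample.
- Two-sided test at 5%, critical value 1.96.
- Efficiency of the Mann–Whitney test relative to the t-test for normal data: 3/π = 0.955, square root 0.977.
- *d*, the shift in the Shannon index caused by age alone, in SD. **Assumed**, from 0 upward.

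Standard error of the standardised difference: √(1/127 + 1/255) = 0.1086.

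Non-centrality: δ = 0.977 × *d* / 0.1086.

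Rejection probability with no antibiotic effect: 1 − Φ(1.96 − δ) + Φ(−1.96 − δ).

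For *d* = 0.1, δ = 0.90 and the probability is 14.7%. For *d* = 0.2, δ = 1.80 and it is 43.6%.

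| *d* (SD, assumed) | 127 v 255 | Simulation, 127 v 255 (4000 runs) | 150 v 300 |
|---|---|---|---|
| 0 | 5.0% | 5.2% | 5.0% |
| 0.05 | 7.3% | not run | 7.8% |
| 0.1 | 14.7% | 15.4% | 16.5% |
| 0.2 | 43.6% | 43.3% | 49.8% |
| 0.3 | 77.0% | 76.8% | 83.4% |

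To give *d* a scale: if the index moved 0.05 to 0.10 SD per day of age, a mean lag of 2 days would give *d* = 2 × 0.05 = 0.1 to 2 × 0.10 = 0.2. Both the slope and the lag are assumptions. A lag of 2 days is hardly credible at T2, which is nominally day two, and there is no basis for carrying a slope from the first two weeks to later samples. With no lag, *d* = 0 and the error rate stays at 5%.

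**The case against.** The strongest reply is that a condensed article need not spell out sampling windows or every covariate, and that the full protocol or the analysis plan may do so. This stands for the windows. It does not settle the rest, because the article names a specific test that cannot carry a covariate and places its confounder models with the clinical endpoints.

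Several stronger readings are tempting, and the text does not support them.

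- *The date will be used only for time since antibiotics.* The article gives one purpose and does not make it exclusive. The date can also yield age.
- *Controls have no time since antibiotics at all.* Later courses are recorded for all infants, so a control can have such an interval. It is undefined only for the early-life course that defines the groups.
- *The groups differ in age at sampling, so the comparison is biased.* No section says so. The schedule is fixed by age, parents receive oral and written instructions, and with controls observed for 24–48 h many T1 and T2 samples should be taken on the ward in both groups.
- *The false-positive rate is 15–44%.* These are outputs of assumed shifts, not estimates for this study.
- *A date alone is too coarse at T1 and T2.* The date-only wording concerns what parents write. Nurses take the first samples, and the article does not say how those are timed.

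**Conclusion.** The point holds as a conditional weakness with an inexpensive remedy. The microbiota comparison is set up at nominal ages, the article gives actual age no role in it, and the named test cannot adjust for age. Whether this biases the result depends on a group difference in age at sampling that is plausible for the early samples but undocumented.

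Under an assumed age-driven shift of 0 to 0.2 SD, the rejection rate of a single comparison with no antibiotic effect runs from 5% to 44% (127 v 255 infants). If ages scatter equally, there is no bias, and the gain from adjusting is precision alone. In either case a comparison that uses actual age is at least as well founded as the one stated.

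**What to change.** 1. For every sample in both groups, derive age in days at collection from the vial date and the date of birth. For samples taken on the ward, confirm where the collection date is held, since the article describes only what parents write.
2. Tabulate actual age by group and time point, with the number of samples. This shows whether a difference exists and whether the groups' ages overlap enough for adjustment to be meaningful.
3. Compare the Shannon index in a regression at each time point, or in a mixed model over all samples with infant as a random effect, including group and actual age. Keep the Mann–Whitney test as a descriptive or sensitivity analysis.
4. For composition, add a distance-based model on the cosine distances with group and actual age as terms, and keep the principal coordinate plots as description.

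Cost: a change of analysis wording and a little more analysis work. The vial date is already requested, and delivery data are already taken from patient records, which should supply the date of birth. No new field on the vials is needed.

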### Outcomes

#### Symptoms via calendar checklist

Parents are instructed to record a (for this study) designed daily checklist of clinical symptoms, which include coughing, wheezing, fever >38 °C, runny nose, glue ear, rash, diarrhea, >3 h of crying within one day (24 h). Table 1 shows the various symptoms, which should be recorded by the parents. Descriptions standardize the way of recording as much as possible. The checklists are designed as a calendar and parents are requested to return a list (at the end of) every month. As a motivation for returning the list, we send back a contemporary Dutch magazine for young parents, monthly, after receiving their list.

**Table 1 Tab1:** Description of symptoms

Coughing	Your infant coughs several times a day and/or has coughing. Regularly there are signs of cold. Don’t record cough because of choking.
Wheezing	During expiration you notice a whistling, wheezy sound coming from the lower airways. During expiration your child is trying to squeeze the air outwards. Don’t record wheezing coming from or through the nose.
Fever >38 °C	Clear from itself, whereby it is important you use a rectal thermometer, measure twice and the temperature is >38 °C on both occasions.
Runny nose	Signs of cold with white/yellow/green mucus running from the nose;
Glue ear	Your child seems to have earache and/or grasps its ear (the ear frequently is high-colored or bends) and/or glue egresses from the ear.
Rash	More than one day existing skin-redness (spots, rash, pimples) on the face, arms or legs, trunk. Disease-symptoms are not necessarily present. The rash can be eczema; eczema mostly is red, moistly, scaly and may itch. Infants cheeks are affected mostly. When children grow up, elbow and knees are preferred sites.
Diarrhea	Increase in stool frequency to twice the usual number per day, that continues more than one day. The content may be watery or mucous.
>3 crying hours a day	Clear from itself, whereby the total crying episodes add up to more than three hours a day (24 h) in total.

At baseline, parents have to fill out an online questionnaire containing questions on demographics, comorbidity and use of medication. This questionnaire includes: gestational age and birthweight of the child, maternal comorbidity (medication during pregnancy and delivery), environmental factors (habitat, housing), parental smoking habits, siblings, pets, chronic diseases and hereditary diseases, ethnicity, education.

Regarding the daily checklists, RTI’s and GITI's are defined as follows: an episode of respiratory tract infection includes at least two consecutive days of coughing and/or wheezing, runny nose and/ or earache (with or without secretion). An episode ends when the child is symptom-free for at least two consecutive days. Diarrhea is defined as increase in stool frequency to twice the usual number per day, during at least two consecutive days. Parents also report visits to the general practitioner because of respiratory or gastrointestinal symptoms of their child (since particularly respiratory infection may have a confounding effect, as antibiotic use and respiratory infections are so common and closely related in early life) [39]. Parents are extensively instructed by one of the investigators, at baseline of the study, how to fill in the daily checklists and how to interpret their child’s symptoms.

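### The parent-reported GITI definition takes no account of concurrent antibiotics, so diarrhea from a later course counts as infection and can inflate the comparison towards the hypothesis

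*Protocol article*

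**What the plan says.** Under Symptoms via calendar checklist, the episode definitions open with "Regarding the daily checklists, RTI’s and GITI's are defined as follows". The only gastrointestinal criterion that follows is "Diarrhea is defined as increase in stool frequency to twice the usual number per day, during at least two consecutive days". Table 1 gives parents the matching instruction: "Increase in stool frequency to twice the usual number per day, that continues more than one day. The content may be watery or mucous". Neither place asks for a sign of infection or mentions antibiotic treatment at the time. Table 1 does screen out look-alikes for other symptoms: for coughing it says "Don’t record cough because of choking", and it also excludes wheeze from the nose. Diarrhea has no such exclusion.

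The same section acknowledges that "antibiotic use and respiratory infections are so common and closely related in early life", and responds by having parents report GP visits.

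The Aims section (text below Fig. 1) predicts a second set of effects beyond eczema. The sentence begins "We also expect an increase in incidence of" and covers food allergy, respiratory tract infections (RTI) and GITI, both parent-reported and doctor-diagnosed. It also says that parents "will report the use of antibiotics (type of antibiotics and duration of treatment) during the complete study period", and that pharmacies will be approached for the first year's medication.

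Under Statistical analysis, later courses are used to group children as 0, 1, or 2 or more. They are not used to classify diarrhea episodes.

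**The concern.** Diarrhea is a recognisable side effect of antibiotics, and the definition cannot tell it from infection. The misclassification arises from courses given after the neonatal treatment that defines exposure, and it can occur in both groups. If both groups had the same number of later courses, it would add noise and dilute a true difference. If the treated group has more later courses, it adds more false episodes there.

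The study's own hypotheses make an imbalance plausible: it expects more RTI in treated infants, and it regards RTI and antibiotic use as closely linked. An RTI excess could then carry over into the GITI count through antibiotic courses. What is at stake is the reading of a GITI excess. It could be taken as more gastrointestinal infection, and as evidence separate from the RTI result, when part of it is neither.

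**Working it through.** The documents state no figure for GITI, so there is none to reproduce. Group sizes come from the Power calculation section: 150 treated and 300 controls less 15% dropout, giving 127.5 and 255 evaluable. Everything else is an assumption.

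**Assumed inputs**
- c, later courses per control infant in the year: 0.4 to 0.8
- a, risk of qualifying diarrhea per course: 0.10 to 0.35
- g, true gastrointestinal infections per infant-year, equal in both groups: 0.7 to 1.0
- r, ratio of later courses, treated to control: 1.3 to 1.5

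**Formulas**
- Share of control GITI that is drug-related = c·a / (g + c·a)
- Null rate ratio = (g + c·r·a) / (g + c·a)

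**Results with no true GITI difference**

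| Case | c, a, g, r | Control share | Null rate ratio |
|---|---|---|---|
| Low | 0.4, 0.10, 1.0, 1.3 | 0.04/1.04 = 0.04 | 1.052/1.04 = 1.01 |
| Middle | 0.6, 0.225, 0.85, 1.4 | 0.135/0.985 = 0.14 | 1.039/0.985 = 1.05 |
| High | 0.8, 0.35, 0.7, 1.5 | 0.28/0.98 = 0.29 | 1.12/0.98 = 1.14 |

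**Against sampling error.** With Poisson counts, the SE of the log rate ratio is √(1/control events + 1/treated events).
- Middle: events 255 × 0.985 = 251 and 127.5 × 1.039 = 132. SE = 0.107, shift = ln 1.055 = 0.053, or 0.5 SE. The false-positive risk of a two-sided 5% test becomes about 8%.
- High: events 250 and 143. SE = 0.105, shift = 0.134, or 1.27 SE. The risk becomes about 25%.
- Overdispersed counts would lower both percentages.

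**As ever/never GITI.** Assume a true risk of 20 to 40% in both groups, later courses Poisson with mean 0.3 to 0.5 in controls and 0.45 to 1.0 in treated infants, and diarrhea risk a of 5 to 30% per course. Then P(GITI) = 1 − (1 − risk)·exp(−a × mean courses).
- Example: risk 0.20, means 0.5 and 0.75, a = 0.10 gives 0.239 and 0.258, an odds ratio of 1.11 and a rejection rate of 7.1%.
- Over the whole grid the odds ratio runs from 1.02 to 1.52 and the rejection rate from 5.1% to 46%. The top values need twice as many courses in treated infants, beyond the 1.3 to 1.5 used above.
- At a = 5% the odds ratio is only 1.02 to 1.12.

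**Across course groups.** For 2 versus 0 courses, P = 1 − (1 − risk)(1 − a)². With risk 0.20:
- a = 0.05 gives 0.278, odds ratio (0.278/0.722)/0.25 = 1.5
- a = 0.30 gives 0.608, odds ratio (0.608/0.392)/0.25 = 6.2

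With risk 0.40 the range is 1.3 to 3.6. This association is built in, with no effect of antibiotics on infection.

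**The case against.** The strongest reply is that tagging rules and sensitivity analyses belong in an SAP, and only a condensed protocol article is shown. That would answer an omission. Here the article says it is defining GITI and then gives a complete rule, and that rule scores drug-related diarrhea as infection.

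Second, GITI is also assessed from GP codes (D70, D10, D73), and disease episodes and antibiotic treatments are discussed and recorded at the one-year visit. The GP-coded endpoint is less exposed and is a useful cross-check. It does not correct the parent-reported endpoint, for which the Aims predict an effect in its own right.

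Third, the planned multivariate models, or a comparison within infants with no later course, might be thought to deal with it. Adjusting for the number of courses leaves the outcome misclassified and conditions on something that may follow from exposure. The zero-course comparison is free of later-course diarrhea but has the same conditioning problem.

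Fourth, GITI is one of several further outcomes and the sample size rests on eczema. That limits the weight of the point and is accepted.

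A reader might infer three stronger things that the documents do not support:
- That an RTI excess must by itself produce a GITI excess. This needs an RTI excess, which is only hypothesised, then more courses, then enough diarrhea per course.
- That later courses are mostly for respiratory infections. The article says only that the two are common and closely related.
- That course dates are stated to be on the calendar. The article lists type and duration. Timing is implied, because investigators plan to calculate the interval between antibiotic treatment and stool sampling.

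**Conclusion.** The point holds as a defect in the parent-reported GITI definition: diarrhea caused by a later antibiotic course is counted as gastrointestinal infection. If treated infants receive more later courses, this can inflate the GITI comparison towards the hypothesis. The direction follows from that one condition. The size rests wholly on assumed inputs: a null rate ratio of 1.01 to 1.14, about 1.05 at mid-range. It would be wrong to conclude that a positive GITI result would usually be this artefact, since at mid-range the false-positive risk rises only from 5% to about 8%. A GITI comparison across the later-course groups is at greater risk. The change is worth making because it is cheap and the bias would favour the expected result.

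**What to change.** State a derivation rule before analysis. Using antibiotic timing from the calendar, checked against pharmacy records, tag each diarrhea episode that starts during a later systemic antibiotic course or within a prespecified window after it. Confirm that the calendar captures start dates as well as duration.

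Report parent-reported GITI twice: with all episodes, and with tagged episodes excluded. In the second analysis also remove the antibiotic-window days from time at risk in both groups. Dropping episodes alone loses more true infections in the group with more courses. For illustration, with a 21-day window, 0.8 control courses and r = 1.5, window time is 0.8 × 21/365 = 4.6% in controls and 1.2 × 21/365 = 6.9% in treated infants. A true ratio of 1 then becomes 0.931/0.954 = 0.98. Removing time at risk needs a rate or time-to-event analysis. Cox regression is already one of the planned options; logistic regression has no time at risk to remove.

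Interpret a GITI excess as infection only if it persists without the tagged episodes, and set it beside the GP-coded result. Apply the same rule to any GITI comparison across course groups.

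The cost is one rule on data largely planned already, slightly fewer events and less time at risk. Some true infections that coincide with a course leave the restricted count; the all-episode analysis still includes them.
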